### Participants

2.2

Participants are being recruited from community centers and non-governmental organizations in Hong Kong using advertisement posters. Eligibility screening for potential participants is conducted via online questionnaires and phone calls. Final enrollment is confirmed during an in-person visit, where participants receive a detailed overview of the study, provide informed consent, and complete a baseline assessment.

Severe cognitive impairment could impair participants’ motor imagery abilities, which may interfere with the assessment of intervention efficacy (26). Therefore, subjects will be included if they are (1) aged 18 years or above; (2) diagnosed with SCI for over 6 months, as per the International Standards for the Neurological Classification of SCI, confirmed by computed tomography or MRI; (3) with stable spinal systems and good vital signs, and residing in the community; (4) having no contraindications for MRI scans (e.g., absence of metal or electronic implants, non-pregnant status, and absence of claustrophobia); (5) having a mobile Internet terminal (usually a smartphone) and proficient independent or caregiver-assisted usage; and (6) able to communicate in Cantonese/Chinese and to provide written informed consent.

The exclusion criteria are as follows: (1) severe impairments in hearing, verbal communication, or vision; (2) participation in concurrent psychotherapy, physiotherapy, exercise, or relaxation interventions; (3) physically active for over 150 min of moderate-intensity exercise per week; (4) diagnosed mental disorders or substance misuse; and (5) severe cognitive impairment [indicated by the Hong Kong Montreal Cognitive Assessment (HK-MoCA) score ≤ 18] (27). No restrictions will be imposed regarding the level, cause, or completeness of the spinal cord injury.

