### Randomization and blinding

2.3

Randomization will be performed through the minimization method (28) to balance the pertinent influencing factors for cognitive function and the intervention effectiveness (i.e., motor imagery ability (29), age, and educational level). Minimization entails assigning intervention to succeeding trial participants based on the characteristics of previously enrolled participants (excluding the first participant who receives a random allocation) to enhance balance among the groups in key variables of interest. An independent administrative clerk will conduct this procedure by using the Minim software and will subsequently provide the researcher with a sequentially numbered, sealed, opaque envelope containing the group assignment for the participants. Due to the nature of the intervention, participants and the researchers who will enroll in the intervention process and qualitative interviews will not be blinded. However, the baseline and outcome assessor, as well as the data analyst, will remain blinded to group assignment.

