### Sample size and sampling

2.6

The central limit theorem posits that a minimal sample size of 30–40 is enough for determining the mean, standard deviations, and 95% confidence intervals (58). This pilot RCT aims to assess the feasibility, acceptability, and preliminary effectiveness of the AOMI intervention, utilizing a generally acceptable sample size for preliminary analysis to evaluate intervention feasibility and estimate the between-group effect. Specifically, each study group will have 18 individuals to identify a standardized effect size of 0.40 with 80% power and a two-sided significance level of 5% (59). Taking into account a potential attrition rate of 20%, 23 participants per group (i.e., 46 participants in total) will be recruited by using convenience sampling. For one-on-one interviews, we will use a purposeful sampling of key informants, including those who completed at least 60% of the intervention sessions and those who did not, until we reach information saturation and find no relevant new codes in the data (60).

For MRI scans, a liberal threshold of *α* = 0.05 requires 24 participants (12 per group) to achieve 80% power at the single-voxel level for typical activations (61). To control error rates in multiple comparisons, doubling the number of participants is recommended to maintain this level of power. Due to the challenges of MRI data collection, each group will consist of a minimum of 12 participants undergoing pre- and post-intervention MRI scans. Notably, this sample size aligns with the median sample size observed in highly cited clinical fMRI studies published over the last three decades (62).

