To analyze fMRI data, differences of each group at baseline and post-intervention will be evaluated using the paired *t-test* in Statistical nonParametric Mapping (SnPM); differences between groups (intervention group vs. control group) will be assessed using a two-sample *t-test*. Differences between the two groups of the study over time will be evaluated using a General linear model, in which group and time will be included as distinct factors (2 × 2 factorial design). Multiple linear regression models will be used, with age, education level, and motor imagery ability as covariates, to assess the correlation between changes in MRI results and changes in cognitive function and depression data after intervention (69). For DTI data, statistical analyses will be performed using non-parametric permutation testing with 5,000 Monte Carlo simulations. We will look for differences in fractional anisotropy between the groups, accounting for age, educational level, and motor imagery ability as regressors of no interest in the general linear model. A two-sample *t* test will be used to evaluate the between-group differences in DTI metrices (e.g., path length, clustering coefficient, global efficiency, local efficiency, strength, and small world attribute). Association analysis between altered white matter microstructure imaging data and the assessments of cognitive function and depression will be analyzed with Spearman’s correlation coefficient (70).

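### The white-matter association with cognition and depression is planned as a Spearman correlation with no covariates, although neighbouring MRI analyses adjust for age, education and motor imagery ability

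*Protocol article*

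**What the plan says.** All of the analyses concerned are in section 2.7.3 of the protocol article.

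- White matter and behaviour, where the method named is Spearman's coefficient: "Association analysis between altered white matter microstructure imaging data and the assessments of cognitive function and depression will be analyzed with". No covariate, partial form or change score is mentioned.
- MRI and behaviour, in the part of the section that deals with fMRI: multiple linear regression "with age, education level, and motor imagery ability as covariates, to assess the correlation between changes in MRI results and changes in cognitive function". The same regression also takes in changes in depression.
- DTI group comparison of fractional anisotropy (FA): a general linear model "accounting for age, educational level, and motor imagery ability as regressors of no interest in the general linear model".

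The three covariates are also the minimization factors. Section 2.3 says they were chosen "to balance the pertinent influencing factors for cognitive function and the intervention effectiveness". Participants must be "aged 18 years or above", with no upper limit stated (section 2.2). On scan numbers, "each group will consist of a minimum of 12 participants undergoing pre- and post-intervention MRI scans" (section 2.6). The MRI analyses are per protocol, restricted to participants who complete at least 60% of sessions.

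**The concern.** The plan adjusts FA for three covariates, and it adjusts an MRI-behaviour association for the same three. It names none of them where white matter and behaviour are related to each other. By the plan's own account, age and education influence cognitive function. If age is also related to the DTI metric, two variables with no direct link will still correlate across participants.

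Minimization does not prevent this. It balances age between the arms and leaves the spread of age among individuals, which is what drives a correlation. Using ranks protects against outliers and non-normality but not against a common cause.

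The stake is interpretation. Section 2.5.3.2 uses MRI to look for mechanisms behind the intervention's effect, and the Discussion wants the findings to support mechanism-driven interventions. A correlation produced by age could be read as such a mechanism.

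**Working it through.** The plan states no figure for this analysis, so there is none to reproduce. The check asks how often the unadjusted test is significant when no direct link exists.

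**Inputs from the article.** n = 24 (2 × 12, section 2.6); two-sided test at 0.05 (section 2.7.1).

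**Assumed inputs.** The correlation of age with the DTI metric (a) and with the cognitive score (b). The article gives neither, so a range is shown. Age, metric and score are taken as normal.

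**Induced correlation.** With no direct link, the metric and the score have Pearson correlation a × b. Under normality the corresponding Spearman value is (6/π) × arcsin(a × b / 2). For a = b = 0.5, a × b = 0.25 and the Spearman value is (6/π) × arcsin(0.125) = 0.24. The simulated mean at n = 24 is 0.23.

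**Simulation, n = 24, levels correlated, no direct link:**

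| Age correlation with metric / score | Mean Spearman rho | Unadjusted test significant |
|---|---|---|
| 0.3 / 0.3 | 0.08 | 6.7% |
| 0.4 / 0.4 | 0.15 | 10% |
| 0.5 / 0.3 | 0.14 | 9.9% |
| 0.5 / 0.5 | 0.23 | 19.7% |
| 0.6 / 0.5 | 0.28 | 26.7% |
| 0.6 / 0.6 | 0.33 | 38% |

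More scans make it worse, because the bias stays and the test becomes more sensitive to it. At 0.5 / 0.5 the rate is 28.3% with n = 36 and 36.2% with n = 46.

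**After adjustment.** A partial Spearman correlation on age, education and motor imagery ability gives 5% to 6% over equal age correlations of 0.3 to 0.6 at n = 24. The degrees of freedom fall from 24 − 2 = 22 to 24 − 2 − 3 = 19.

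**Change scores.** If changes are correlated and age acts on levels only (0.5 with each), age cancels in the subtraction. The mean rho is 0.00 and the unadjusted test rejects in 5.2% of trials. The inflation therefore needs either levels, or an effect of age on the changes themselves.

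**The case against.** The strongest reply is that the article does not fix levels or changes. The word altered may point to change, although it may equally mean tracts that differ between groups. The section's other MRI-behaviour association is explicitly change on change. If the Spearman analysis is too, and age acts on levels only, there is no bias. This stands, and it makes the concern conditional. It does not remove it: section 2.3 lists age and education as factors for intervention effectiveness as well, and the plan's own change regression still adjusts for them.

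Second, that regression refers to MRI results in general and might already cover DTI. Its position before the DTI sentences suggests otherwise. If it does cover DTI, the article has an adjusted and an unadjusted analysis of the same question and does not say which governs.

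Third, a full protocol or analysis plan could specify a partial form. That the correlation is unadjusted is inferred from the absence of any covariate, in a section that names covariates elsewhere.

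Three stronger readings are tempting but unsupported:

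- A reader might infer that FA is adjusted because age affects white matter. The article gives no reason. The covariates are the minimization factors, which explains the choice equally well.
- A reader might extend the argument equally to depression. Section 2.3 ties age and education to cognitive function and intervention effectiveness, not to depression.
- A reader might take the upper rates as expected. They rest on assumed correlations, the low end is close to nominal, and excluding HK-MoCA scores of 18 or below may weaken the relation of age to cognition.

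**Conclusion.** The concern holds in conditional form. The section names an unadjusted method for one MRI-behaviour association while adjusting the other, and FA itself, for three covariates. If levels are correlated, or if age also drives the changes, the nominal 5% test rejects in about 7% to 38% of trials with no direct link. This assumes n = 24 and age correlations of 0.3 to 0.6 with each variable. With change scores and age acting on levels only, the rate stays at about 5%.

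Support is best for cognition. The analysis is exploratory, per protocol and part of a pilot. It does not affect the primary outcomes, the feasibility criteria or the group comparisons, so the point does not bear on whether AOMI is judged to work.

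**What to change.** Replace the Spearman sentence with a partial rank correlation (or rank regression) of change in the DTI metric with change in NUCOG or BDI-II, adjusted for age, education and motor imagery ability. State explicitly that changes are used and how the two arms are handled. If the adjusted regression in the fMRI part is meant to cover DTI, say so and state which analysis governs.

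The cost is a sentence or two of analysis wording and three degrees of freedom in a sample of about 24. All the variables are already collected at baseline.

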#### Qualitative data analysis

2.7.4

Content analysis will be conducted on qualitative data generated through one-on-one interviews. Research assistants will transcribe the recorded interviews and send them to the participants for verification. Two researchers with a background in qualitative data analysis will independently code the transcripts and cross-check them. Categories/subcategories and themes/subthemes will be gradually formed through repeated discussions in the research group (71).

### Patient and public involvement

2.8

Patients and/or the public did not and will not engage in the design, execution, or reporting of this research. Participants will be invited to provide post-intervention evaluations. Qualitative interview findings will undergo participant validation, while both participants and clinicians will contribute to disseminating research outcomes within their professional networks (31).

### Ethics and dissemination

2.9

This trial follows the Declaration of Helsinki and has been approved by the Institutional Review Board of the Hong Kong Polytechnic University (HSEARS20240716007-01). All eligible subjects will be asked to participate after receiving an explanation of the aim of the study, the potential benefits and risks, confidentiality and autonomy issues, and the right to withdraw at any time. Eligible subjects who agree to participate will be asked to sign a consent form before the baseline assessments of the study (Supplementary material, consent form). In addition, the consent forms will also be obtained from participants who will accept MRI scans and one-on-one interviews. If any safety concerns emerge in the process, the participants will be evaluated and managed by our research team (we have a physiotherapist and nurses in our team). If participants experience severe dizziness, fatigue, pain, injury, or illness during the intervention, they can immediately withdraw from the study and be referred to healthcare professionals for further assessment and care. The study results will be disseminated in peer-reviewed journals and conference presentations. The researcher will report only aggregate findings, not individual data, to the public.

## Discussion

3

This study focuses on cognitive impairment and depression, both of which are significant issues in adults with SCI that have not yet been well addressed. Although physical exercise-based interventions have shown preliminary efficacy for these two conditions in SCI, their clinical application remains limited to individuals with certain levels of motor function (72). Conversely, AOMI exhibits comparable therapeutic benefits while accommodating a broader SCI population, including those with severe motor impairments (16, 18). Furthermore, AOMI can be self-administered following proper training. Emerging evidence supports the positive effects of AOMI on other disabled cohorts. This study will be the first to specifically develop and explore the therapeutic potential of a home-based AOMI intervention for improving cognitive function and depression following SCI. Additionally, it will further evaluate the efficacy of improving attention and executive function, two cognitive domains particularly vulnerable in individuals with SCI and crucially associated with successful community reintegration (20).

In recent years, few studies have implemented AOMI for SCI survivors targeting pain relief (73). While its feasibility has reached consensus, the therapeutic effects remain controversial. Given that pain represents a risk factor for both primary outcomes, this study will additionally examine whether AOMI might indirectly enhance cognitive function and reduce depression in adults with SCI through pain modulation. Following SCI, individuals frequently experience diminished exercise self-efficacy, leading to lower physical activity levels and subsequent negative impacts on both cognitive function and mood (74). While prior research has established AOMI’s positive effects on exercise self-efficacy in healthy populations and athletes (75), this study specifically evaluates its efficacy in adults with SCI. If these positive effects are preliminarily demonstrated, this home-based AOMI could offer a non-invasive, accessible, cost-efficient new path to the healthcare plans of SCI rehabilitation.

This pilot RCT adopts a multidisciplinary approach, incorporating psychological, neurological, and neuropsychological assessments. The utilization of multimodal MRI enables a better understanding of the neural mechanism behind the AOMI and post-SCI neuroplastic changes. These findings will establish an empirical foundation for developing mechanism-driven interventions targeting cognitive impairment and depression in adults with SCI.

This study has several limitations that should be acknowledged. First, this pilot RCT can only show the preliminary effectiveness of the home-based AOMI intervention. Furthermore, the small sample size and potential selection bias resulting from convenience sampling may limit the generalizability of the findings. However, the results of this pilot study will provide valuable insights for designing a future full-scale RCT, which could generate much-needed level one evidence regarding the effectiveness of AOMI. Second, due to the inherent nature of the intervention, neither the interventionists nor the participants could be effectively blinded. Although we will implement weekly phone monitoring of intervention adherence and design an active control condition, potential performance bias may remain a limitation. Third, a defining characteristic of AOMI is the absence of overt physical actions during the imagery process. This inherent feature makes objective performance evaluation challenging, as AOMI relies on mental movement representation. We will employ qualitative methods (i.e., training diaries and post-intervention interviews) to assess whether participants really engaged in AOMI and whether they truly imagined the intended content. However, integrating objective methods such as neuroimaging techniques would better evaluate intervention fidelity. Due to resource constraints, we will consider this monitoring method in future research.
